## Abstract

**Background:**

Virtual reality exposure therapy (VRET) has been shown to be as effective as traditional forms of in vivo exposure therapy for the treatment of specific phobias. However, as with in vivo exposure, VRET still involves relatively high costs and limited accessibility which makes it prohibitive for a large part of the population. Innovative methods using smartphone applications (apps) may improve accessibility and scalability of VRET. The aim of this study is to evaluate 0Phobia, a gamified self-guided VRET for acrophobia that is delivered through a smartphone app in combination with rudimentary cardboard virtual reality (VR) goggles.

**Methods/design:**

Participants (*N* = 180, aged 18–65 years) with acrophobia symptoms will be recruited from the Dutch general population and randomized to either 0Phobia (*n* = 90) or a waitlist control condition (*n* = 90). 0Phobia will be delivered over a period of 3 weeks and includes psychoeducation, VR exposure, cognitive techniques, monitoring of symptoms, and relapse prevention. The primary outcome measure will be the Acrophobia Questionnaire. Secondary outcome measures will include user-friendliness, symptoms of anxiety, depression, and mastery. Assessments will take place online at baseline, directly after the intervention (post test) and at follow-up (3 months).

**Discussion:**

This study capitalizes on novel technology and recent scientific advances to develop an affordable and scalable treatment modality.

**Trial registration:**

Netherlands Trial Register: NTR6442. Registered on 29 June 2017.

**Electronic supplementary material:**

The online version of this article (10.1186/s13063-018-2704-6) contains supplementary material, which is available to authorized users.

## Background

With lifetime prevalence estimates of between 8 and 15% [1, 2], specific phobias rank among the most prevalent mental disorders, along with depressive disorders and social phobia [3]. The lifetime prevalence of specific phobias in the Netherlands is nearly 8%. Around 530,000 people in the Netherlands currently suffer from one or more specific phobias and each year there are 75,000 new cases with a specific phobia diagnosis [3]. In the general EU population, 18.5 million people are estimated to suffer from a specific phobia [4]. Acrophobia is the most prevalent of all specific phobia subtypes [5, 6]. Due to high treatment costs, long waiting lists, and a general reluctance to seek treatment [7], access to evidence-based therapy is currently limited. If left untreated, specific phobias can become chronic and increase the risk of developing other mental disorders, such as anxiety and depression, especially for women [8]. Given the psychological burden that phobias carry, along with an increased risk of developing comorbid depressive and anxiety disorders, and the economic burden for society [9], there is an evident need for affordable and scalable self-help interventions.

Specific phobias have a lengthy history of clinical research and effective treatment exists [10]. In exposure therapy a person is gradually exposed to the object or situation of their fear. Meta-analyses have repeatedly demonstrated the effectiveness of exposure to reduce anxiety levels of specific phobias in different settings (e.g., [10, 11]). In fact, exposure therapy is among the most effective treatments existing in psychological health care [10].

### Virtual reality exposure therapy (VRET)

Over the past decades, a new type of treatment based on the principles of exposure therapy has emerged. This new form of exposure therapy relies on virtual reality (VR) rather than exposure “in vivo.” In VRET, artificially created computer-generated environments replace real-life settings. Individual studies as well as meta-analyses on treatment effectiveness for people suffering from anxiety disorders, and specific phobias in particular, have shown VRET to be as effective as traditional forms of exposure therapy in reducing anxiety (e.g., [12–17]). For example, in a recent meta-analysis of 14 studies [13], participants in the VRET condition for specific phobias improved significantly on behavioral assessments after VRET from pre to post test (aggregated uncontrolled effect size *g* = 1.23) as well as when compared with waitlist control subjects (*g* = 1.41). Additionally, there were no significant differences in terms of effectiveness between VRET and exposure in vivo at post test and follow-up (*g* = − 0.09 and 0.53, respectively), although results should be interpreted with caution as these studies were not adequately powered. Furthermore, in a meta-analysis by Opriş et al. [16], results demonstrated that VRET has better outcomes than waitlist controls, similar efficacy for VRET and cognitive behaviour therapy (CBT), and no difference in dropout rate between VRET and traditional exposure in vivo.

Aside from demonstrated effectiveness for anxiety disorders, and specific phobias in particular, VRET has a number of additional advantages over traditional “in vivo” treatment, such as the possibility to conduct it within the confines of the therapist’s office rather than having to go outside. Furthermore, VRET offers more flexibility in terms of sequencing, intensity of treatment, and graduality of exposure [18]. That is, people can practice more often and with a larger variety of scenarios compared to in vivo exposure, which may optimize exposure therapy [19]. Also, in VR, serious gaming elements can be integrated during exposure, which may reduce distress as compared with traditional exposure therapy [20]. Continuous confrontation with phobic stimuli may be facilitated by a gamified VR content that can be played repeatedly [20, 21].

Nonetheless, in spite of having several advantages over traditional in vivo therapy, VRET still involves relatively high costs and limited accessibility which make it prohibitive for a large part of the population. Existing VRETs tend to require heavy graphic processing capabilities not found in ordinary computers and mobile devices. Finally, and importantly, existing VRETs still require the intervention of a therapist.

### Mobile app interventions

Recent research has demonstrated the efficacy of mobile-app-based therapies for anxiety and depression [22, 23]. App-based mental health interventions based on CBT principles have shown to be effective in reducing mental health symptoms (e.g., [23] for a review) and guided Internet interventions have proven potential to be cost-effective ([24] for a review, [25]).

Advantages of app-based interventions compared to traditional therapy include high accessibility, real-time progress monitoring, portability, flexibility, and cost-effectiveness [26]. To the best of our knowledge, so far only one study has investigated the effectiveness of guided VRET using a mobile application and VR goggles. This intervention led to a significantly reduced fear of spiders [27], although older technology (red/blue anaglyph glasses and a computer monitor) was used. Another study, in which the effectiveness of guided VRET on a smartphone and VR goggles compared with traditional one-session exposure therapy for subjects with spider phobia, is currently being evaluated [21]. To our knowledge, no studies have yet explored the feasibility and efficacy of (1) self-guided VRET delivered through a smartphone app using (2) low-cost VR goggles for acrophobia. Instead of high-end head mounted displays (e.g., Samsung Gear VR), we use rudimentary 10-dollar cardboard VR goggles. The aim of this project is to test a self-guided, stand-alone treatment modality for acrophobia symptoms through exposure therapy by integrating VR technology with a smartphone app. The acrophobia intervention will be tested for user-friendliness as well as its effectiveness in reducing acrophobia symptoms for adults from the general Dutch population with acrophobia symptoms using a randomized controlled trial (RCT) design. We hypothesize that participants in the experimental condition will show a significant reduction in acrophobia symptoms at post test and follow-up compared to baseline and significantly less acrophobia symptoms than the waitlist control condition.

## Methods/design

### Study design

A RCT will be carried out, in which the efficacy and user-friendliness of a self-guided, 3-week, mobile-app-based VR self-guided treatment “0Phobia” will be evaluated. In total, 180 participants from the Dutch general population will be randomized to two conditions: the experimental condition (0Phobia; *n* = 90) and a waitlist condition (*n* = 90). Measures will be taken at baseline and directly after the intervention (post test). After post-test assessment, the waitlist group will be granted access to the intervention. The experimental condition will receive a final follow-up questionnaire 3 months after baseline (follow-up). All measures will be completed online. Two reminders will be send (one by email, one by telephone) if necessary. This study has received ethical approval by the Medical Ethics Committee of the VU University Medical Center (registration number 2016–563) (Trial registration: NTR 6442). Figure 1 presents the flowchart of the study.

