### Sample size

The primary outcome measure, the AQ, has been used for the power calculations. In previous RCTs using the AQ as an outcome measure, effect sizes of 0.79–1.42 [14, 15] were demonstrated. However, as the present intervention will use low-end cardboard VR goggles instead of expensive head-mounted displays, the current study uses a more conservative estimate for the post-treatment effect on the AQ. In order to detect a difference between the experimental and the waitlist control condition with a standardized effect size (Cohen’s d) of 0.50 (two-sided), an alpha of 0.05 and statistical power (1 − *β*) of 0.80, we need 64 participants in each condition (128 participants in total). With an anticipated dropout of 40%, this requires a total target sample size of 180 participants.

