### Randomization, blinding, and treatment allocation

A randomization list will be created with Random Allocation Software using block randomization of 6, 8, 10, and 12 blocks at an allocation ratio 1:1. Participants will be randomized into two groups: experimental or waitlist condition. The randomization list is kept by an independent researcher. This person reveals the next randomization outcome after every inclusion and thus ensures that the researchers are blind for treatment allocation. Due to the nature of the study, it is not possible to blind the participants for the randomization outcome.

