### Assessments

#### Primary outcome measure

##### Acrophobia questionnaire

The main outcome measures will be the 20-item anxiety subscale and the 20-item avoidance subscale of the Acrophobia Questionnaire (AQ; [28]). The AQ is a widely-used instrument with good psychometric properties [28]. The anxiety subscale is measured using a 7-point Likert scale (0 = not anxious to 6 = extremely anxious), total score range 0–120. The avoidance subscale uses a 3-point Likert scale (“I would not avoid it” to “I would not do it under any circumstances”). Both subscales will be taken at baseline, directly after finishing the modules, at post test, and at follow-up. See Fig. 3. 

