##### Igroup Presence Questionnaire

The Igroup Presence Questionnaire (IPQ; [40]) is a 14-item questionnaire which assess realism and “presence,” i.e., the subjective feeling of being immersed in the virtual environment. Each of the items has five response categories from 1 = fully disagree to 5 = fully agree. Internal consistency is adequate. This questionnaire along with some open questions about user experience of the VR environment will be completed at post test.

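### The plan expects 40% dropout on the AQ but states no step to obtain the AQ alone from a participant who declines the full post test

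*Protocol article*

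**What the plan says.** - **Primary outcome** (Assessments, Acrophobia questionnaire): "The main outcome measures will be the 20-item anxiety subscale and the 20-item avoidance subscale of the Acrophobia Questionnaire". That is 40 items.
- **Expected loss** (Sample size): 64 evaluable participants per arm, 128 in total, for d = 0.50, two-sided alpha 0.05 and power 0.80. Then: "With an anticipated dropout of 40%, this requires a total target sample size of 180 participants".
- **Retrieval** (Study design): all measures are online, and "Two reminders will be send (one by email, one by telephone) if necessary".
- **Delivery** (Procedure): participants get a link to the post test when the intervention ends. The waitlist arm gets the app after completing that post test.
- **Rest of the post test** (Assessments): ATHQ, BAI, SUS, IPQ, mastery scale, PHQ-9, and short sets on professional treatment, cybersickness, vision and real-life practice. Open questions come with the IPQ: "This questionnaire along with some open questions about user experience of the VR environment will be completed at post test".
- **AQ-only contact** (Procedure; Data monitoring and management): app users who finish module 6 before the three weeks are over are sent a separate AQ link, to estimate the effect of the VR exposure.
- **Missing data** (Statistical analyses): a table comparing those with and without outcomes, Lee bounds, imputation from pre-scores and background characteristics depending on those results, and app usage data to model missingness. The primary analysis is intention-to-treat.

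**The concern.** A trial that budgets for losing two in five primary outcomes has good reason to protect that outcome separately from the secondary scales. Here the AQ is part of a long battery, and the stated retrieval effort is one email and one telephone call. Nothing describes what happens when a participant reached by telephone will not do the whole battery but might do the AQ.

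The AQ link after module 6 does not fill this gap. It reaches only app users who finish early, who are probably among the least likely to be lost. It does not reach app users who do not finish, or the waitlist arm before its post test.

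Power is at stake, and so is how far the intention-to-treat result rests on bounds or imputation: at the planned loss, 0.40 × 180 = 72 of 180 AQ outcomes would be missing. Lee bounds limit the possible bias and imputation models the loss, but neither supplies the outcome. App usage data can inform a missingness model in the app arm only, because the waitlist arm has no app before post test.

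**Working it through.** **Inputs.** From Sample size: d = 0.50, two-sided alpha 0.05, power 0.80, 64 per arm, 40% dropout, N = 180. From Randomization: 1:1 allocation, so 90 per arm. Item counts come from Assessments. The recovery rate r is an assumption, shown as a range.

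**1. The plan's own figures.** A two-sample t-test with these inputs needs 63.8 per arm, rounded up to 64, or 128 in total. This reproduces. For dropout, 128 × (1 + 0.40) = 179.2, rounded up to the stated 180. To have 128 left after 40% loss needs 128 / (1 − 0.40) = 213.3, or 214. So 180 covers a loss of at most 1 − 128/180 = 28.9%.

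**2. Power at the planned loss.** Observed n per arm = 90 × 0.60 = 54, with 36 missing. The noncentrality is d × √(n/2) = 0.50 × √27 = 2.60. Power is 73.1% by the t-test (73.8% by the normal approximation).

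**3. Power with recovery.** If a share r of the 36 missing per arm gives the AQ, n = 54 + 36r.

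| r (assumed) | n per arm | Power (t-test) |
|---|---|---|
| 0 | 54 | 73.1% |
| 10% | 57.6 | 75.8% |
| 25% | 63 | 79.5% |
| 50% | 72 | 84.6% |

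Returning to 64 per arm needs 10 of the 36, about 28%.

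**4. Battery length.** App arm: AQ 40 + ATHQ 6 + BAI 21 + SUS 10 + IPQ 14 + mastery 7 + PHQ-9 9 + treatment 2 + cybersickness 3 + vision at least 1 + practice 2 = 115, plus open questions. If SUS, IPQ, cybersickness and vision are not given to the waitlist arm, its count is 115 − (10 + 14 + 3 + 1) = 87. The article does not state that restriction; it is inferred from what the scales ask.

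**5. Bias in one arm's observed-case mean.** Let D be the difference in mean between the original responders and the original non-responders. With 40% missing, the bias is 0.40 D. Two cases for those recovered:

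- *A random sample of the non-responders.* The missing fraction becomes 0.40(1 − r), and the gap between the enlarged observed group and those still missing shrinks to 0.60 D / (0.60 + 0.40r). The bias is their product:
  - r = 10%: 0.36 × 0.60 / 0.64 = 0.34 D
  - r = 25%: 0.30 × 0.60 / 0.70 = 0.26 D
  - r = 50%: 0.20 × 0.60 / 0.80 = 0.15 D
- *People who resemble the original responders.* The observed mean does not move and the bias stays at 0.40 D.

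These figures describe an observed-case mean in one arm. They are not the bias of the treatment contrast under the planned bounds or imputation.

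**The case against.** The strongest reply is that this is a condensed article. Scale order, handling of partly completed surveys and the telephone script usually sit in a fuller document, and the article already plans two contact modes, one of them personal. Several parts of this reply stand.

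- **Lost data are not stated.** A reader might infer that everyone willing to give only the AQ is lost. The article does not say that partial surveys are discarded, that the AQ comes late, or that the caller would refuse the AQ alone. What can be said is that no step to obtain it is stated.
- **The power gap has another source.** With 214 randomised, the same reminders and the same 40% loss would meet 80%. Weak retrieval does not cause the shortfall.
- **Attrition bias is a risk, not a result.** A reader might infer that the intention-to-treat estimate will be biased, or that recovery must reduce bias. The plan has bounds and imputation for this, and step 5 of the working shows a case with no reduction at all.
- **Burden is not shown to be the cause of dropout.** The article gives no reason for the 40%, and the 115 against 87 split rests on an assumption. Giving the waitlist arm the app after its post test may also be an incentive to respond there, so the net difference in loss between arms cannot be read from battery length.

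The reply does not remove the core. The article does describe its retrieval step, that step contains no AQ-only fallback, and the one AQ-only link goes to a group that is not the problem.

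**Conclusion.** The point holds as a cheap and worthwhile improvement, not as an error that invalidates the design. With 40% dropout expected, the article states two reminders for a single long post test and no fallback for the primary outcome alone.

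At that loss, power at d = 0.50 is about 73%. If an AQ-only request recovered 10%, 25% or 50% of the missing, power would be about 76%, 80% or 85%; about 28% recovery is needed to pass 80%. These figures assume equal loss in both arms and an analysis of observed AQ scores. The recovery rates are illustrations, as the article gives no basis for them. The gain in power follows from the extra observations, while any gain against bias depends on who responds. The dropout inflation needs its own correction, for which better retrieval is only a partial remedy.

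**What to change.** Apply the following identically in both arms:

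1. Place the AQ first in the post test, and keep and analyse partly completed surveys. If this is already the practice, say so.
2. At the planned telephone reminder, ask for the full battery first. Only if the participant declines it, send an AQ-only link.
3. Use these AQ scores in the primary intention-to-treat analysis, and report how many came by this route in each arm.

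**Cost.** One short survey link and a line in the reminder script. The call is already planned and an AQ-only survey already exists for the contact after module 6, so no extra staff are needed. The article describes a route for amendments and reports recruitment as ongoing at submission.

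**Downside.** These participants give no secondary outcomes, their AQ scores arrive slightly later, and some may choose the short form who would otherwise have completed the full battery. Offering it only after a refusal limits that last effect.

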**Fig. 1 Fig1:**
[figure not shown]
Study flowchart

### Procedure

Advertisements with a call to participate in a VR mobile app study for acrophobia will be posted on several websites (e.g., proefpersonen.nl, Facebook) and in magazines (e.g., VU magazine). Media coverage in national television and radio broadcasts will provide additional publicity for the study. Potential participants are directed to the study website (http://www.0-phobia.nl) where information about the study is provided including eligibility criteria. Interested participants can leave their contact details at the website. The research team will send them a screening questionnaire to assess eligibility. Ineligible participants will be automatically directed to a screen explaining why they cannot participate in the study. The screening questionnaire assesses level of depression and suicidal thoughts, inclusion and exclusion criteria only. Participants excluded as a result of high levels of depression are advised to contact their general practitioner (GP). In case of high risk for suicide, participants are contacted by telephone by a member of the research team. The participant will be asked for permission to contact their GP.

Eligible participants receive an information letter and consent form with a return envelope. If necessary, they will be reminded by email to complete the informed consent (two reminders in total). After receiving the signed consent form, participants are invited to fill out an online screening battery. After completion, an independent researcher will assign participants to either the experimental condition or the waitlist condition based on the randomization list which is created by using Random Allocation Software. The participants will be send an email stating to which condition they are assigned. Participants assigned to the intervention condition will be sent the VR goggles by postal delivery – along with user instructions for the VR goggles, instructions to conduct the VR sessions (e.g., to start sitting and when anxiety decreases to stand up, to remove sharp objects in their vicinity to avoid injury, to practice each day at a set time), and instructions on how to download and use the 0Phobia app.

The app is accessed with a unique individual code on the participant’s own smartphone. Once the app is installed, participants can begin with 0Phobia intervention which they can follow for 3 weeks at their own pace. During this 3-week period participants receive weekly motivational emails with information reminding them to start or continue with 0Phobia to increase intervention adherence. These emails will be sent unconditional of app activity.

If participants have questions or experience severe distress, they are encouraged to contact the research team.

After module 6, participants are encouraged to seek out heights in real life. Therefore, participants who finish 0Phobia who have finished module 6 earlier than the 3 weeks will receive an email with a link to the Acrophobia Questionnaire (AQ [28]) in order to obtain estimates of the treatment on levels of acrophobia through VR exposure.

Directly following the conclusion of 0Phobia, participants are sent a link to the online post test. After completing the post test, the waitlist condition will be granted access to the 0Phobia therapy. After 3 months, participants in the experimental condition are asked to fill in the follow-up questionnaire.

### Inclusion and exclusion criteria

A sample of 180 individuals (aged 18–65 years) with symptoms of acrophobia will be recruited among the Dutch population. Inclusion criteria are a sufficient level of AQ-Anxiety (AQ score of 45.45, which is one standard deviation below the mean of a previous acrophobic sample; [28, 29]) having access to an Android smartphone (Android v.5.1 Lollipop or higher, 4.7–5.5-in. screen and gyroscope) with Internet, and having provided informed consent. Participants outside the 18–65 years age range, participants with insufficient knowledge of the Dutch language, those under treatment for a specific phobia or taking psychotropic medication (unless on stable dosage for the previous 3 months and no changes planned during the study period), and participants with symptoms of severe depression (Patient Health Questionnaire (PHQ-9); total score > 19) or suicidality (Web Screening Questionnaire; WSQ, score 3; [30]), are excluded from participation. Suicidal ideation will be measured using one item about suicidal ideation from the Screening Questionnaire [31] that has been translated for the Dutch population in the WSQ [30]: “has the idea of harming yourself, or taking your own life, recently come into your mind?” Answer options are: (1) “Definitely not”; (2) “I seriously considered it but I stopped myself”; (3) “I would do it given the opportunity.” Participants with a score of 3 will be excluded from participation and will be contacted by a member of the research team.

